**Concomitant medication Table Page 2 (only if any symptoms with grading 3 or 4 occurred)**

| **Name of Drug**  **(please use a new row for each drug)** | **Dose** | **Unit** | **Freq (number of times per day)** | **Route** | **Date Started (dd/mm/yy)** | **Date Stopped (dd/mm/yy)**  **Or Continuing?** | **Indication**  **(please make sure that this is in accordance with the symptoms table)** |
| --- | --- | --- | --- | --- | --- | --- | --- |
|  |  | ☐ mg  ☐ g  ☐ ml  ☐ mcg  ☐ drops  ☐tsp  ☐tablet/capsule  ☐don’t know  ☐ other:_____ |  | ☐ oral  ☐ topical  ☐ IM  ☐ rectal  ☐ IV  ☐ don’t know  ☐ other : ________ | _ _ / _ _ / _ _ | _ _ / _ _ / _ _  ☐Continuing |  |
|  |  | ☐ mg  ☐ g  ☐ ml  ☐ mcg  ☐ drops  ☐tsp  ☐tablet/capsule  ☐don’t know  ☐ other:_____ |  | ☐ oral  ☐ topical  ☐ IM  ☐ rectal  ☐ IV  ☐ don’t know  ☐ other : ________ | _ _ / _ _ / _ _ | _ _ / _ _ / _ _  ☐Continuing |  |
|  |  | ☐ mg  ☐ g  ☐ ml  ☐ mcg  ☐ drops  ☐tsp  ☐tablet/capsule  ☐don’t know  ☐ other:_____ |  | ☐ oral  ☐ topical  ☐ IM  ☐ rectal  ☐ IV  ☐ don’t know  ☐ other : ________ | _ _ / _ _ / _ _ | _ _ / _ _ / _ _  ☐Continuing |  |

**Concomitant medication Table Page 3 (only if any symptoms with grading 3 or 4 occurred)**

| **Name of Drug**  **(please use a new row for each drug)** | **Dose** | **Unit** | **Freq (number of times per day)** | **Route** | **Date Started (dd/mm/yy)** | **Date Stopped (dd/mm/yy)**  **Or Continuing?** | **Indication**  **(please make sure that this is in accordance with the symptoms table)** |
| --- | --- | --- | --- | --- | --- | --- | --- |
|  |  | ☐ mg  ☐ g  ☐ ml  ☐ mcg  ☐ drops  ☐tsp  ☐tablet/capsule  ☐don’t know  ☐ other:_____ |  | ☐ oral  ☐ topical  ☐ IM  ☐ rectal  ☐ IV  ☐ don’t know  ☐ other : ________ | _ _ / _ _ / _ _ | _ _ / _ _ / _ _  ☐Continuing |  |
|  |  | ☐ mg  ☐ g  ☐ ml  ☐ mcg  ☐ drops  ☐tsp  ☐tablet/capsule  ☐don’t know  ☐ other:_____ |  | ☐ oral  ☐ topical  ☐ IM  ☐ rectal  ☐ IV  ☐ don’t know  ☐ other : ________ | _ _ / _ _ / _ _ | _ _ / _ _ / _ _  ☐Continuing |  |
|  |  | ☐ mg  ☐ g  ☐ ml  ☐ mcg  ☐ drops  ☐tsp  ☐tablet/capsule  ☐don’t know  ☐ other:_____ |  | ☐ oral  ☐ topical  ☐ IM  ☐ rectal  ☐ IV  ☐ don’t know  ☐ other : ________ | _ _ / _ _ / _ _ | _ _ / _ _ / _ _  ☐Continuing |  |

**Did the patient take any traditional medicines along with PQ at the time of treatment or in the two-week period prior to the onset of the event?**

**☐ Yes ☐No**

*If yes, give details if known:* **______________________________________________________________________________________________________________________________________________________________________________________________________________**

**End of study assessment**

The patient completed follow up until day 16 ☐ Yes ☐No

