**A study to assess primaquine treatment guidelines on malaria in south-east Bangladesh**

**PI: [name]**

**Co-PIs: [name], [name], [name], [name], [name], [name]**

**Version 2.1**

| **SYNOPSIS** |  |
| --- | --- |
| **Title** | **A study to assess primaquine guidelines on malaria treatment in south-east Bangladesh** |
| **Protocol Number** | *--to be added--* |
| **Methodology** | Observational Study |
| **Study Duration** | *P.falciparum* patients to be followed for 30 days  *P.vivax* patients to be followed for 30 days |
| **Country** | Bangladesh |
| **Study Centre** | Alikadam |
| **Primary Objective** | - To assess side effects observed following unsupervised PQ treatment in *P. vivax* and *P. falciparum* patients |
| **Secondary Objectives** | - To assess the schizontocidal efficacy of 3 days Chloroquine (CQ) for *P. vivax* - To assess parasite clearance rates in P*. falciparum* patients treated with artemether-lumefantrine (AL) - To determine the risk of haemolysis associated with G6PD activity - To determine the distribution of G6PD activity and genetic variants among malaria patients - To determine parasite related factors that may affect treatment outcome |
| **Inclusion Criteria** | - Age ≥ 12 months - *P. vivax* or *P. falciparum* monoinfection or *P.v.* / *P.f.* mixed infection - Presence of axillary temperature ≥ 37.5°C or history of fever during the past 24 hrs - Ability to swallow oral medication. - Ability and willingness to comply with the study protocol for the duration of the study - Informed consent/assent from the patient or from a parent or guardian in the case of children. |
| **Exclusion Criteria** | - Presence of general danger signs in children aged under 5 years or signs of severe malaria according to the definitions of WHO - Presence of severe malnutrition - Acute anaemia <8g/dL - Regular medication, which may interfere with antimalarial pharmacokinetics - History of hypersensitivity reactions or contraindications to any of the drug(s) tested or used as alternative treatment(s) - A positive pregnancy test or lactating - Severe G6PD deficient patients will be excluded from PQ treatment |

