**Table: Maximum amount of venous blood collected on d0 / body weight**

| **Patient’s approximate weight in kilograms** | **Amount (mL)** |
| --- | --- |
| >6 to 7 | 4-5 |
| >7 | 5 |

All participants will be followed daily until day 2 to provide supervised treatment and ensure clinical and parasitological recovery following chloroquine (Pv arm) or artemether-lumefantrine (Pf arm and Pf/Pv arm) treatment.

Thereafter patients (excluding those with severe G6PD deficiency) will be given unsupervised primaquine for 1 dose (Pf arm) or 14 doses (Pv/mix arm) and reviewed again after 7 days (day 9), 14 days (day 16), 21 days (day 23) and 28 days (day 30). All P. vivax and mixed infections will in addition be followed up after 3 and 10 days (day 6 and 12 respectively) to assure the safety of the provided treatment. Any patient developing signs and symptoms indicative of a malarial episode or an adverse event within the follow up period will be asked to re-attend the clinic for an unscheduled visit, where they will be offered clinical management according to local clinic guidelines. A fingerprick will be performed during every follow up and unscheduled visit, 5ml of blood will be collected for every recurring malaria episode (see table below). Information on adverse events will be collected during every visit. Whenever possible a pill count will be performed on day 16.

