## Concomitant treatment

Patients under regular medication at trial entry for conditions other than malaria, will have this documented on the CRF and will be asked to continue medication as usual. Any additional medications taken within the follow-up period must be documented in the CRF. Patients who prematurely discontinue trial medication, or who fail to respond to trial medication and receive other anti-malarial therapy will have this documented. Drugs with antimalarial activity should be avoided (Annex I).

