## Efficacy endpoints

- Proportion of patients with any parasitemia on day 1, 2 and 3 after treatment
- Proportion of patients with fever on day 1, 2 and 3 after treatment
- Recurrence of parasitaemia within 30 days of follow up
- Proportion of Pf patients with gametocytemia on any of the follow up dates.

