**Concomitant medication Table Page 1 (only if any symptoms with grading 3 or 4 occurred)**

| **Name of Drug**  **(please use a new row for each drug)** | **Dose** | **Unit** | **Freq (number of times per day)** | **Route** | **Date Started (dd/mm/yy)** | **Date Stopped (dd/mm/yy)**  **Or Continuing?** | **Indication**  **(please make sure that this is in accordance with the symptoms table)** |
| --- | --- | --- | --- | --- | --- | --- | --- |
|  |  | ☐ mg  ☐ g  ☐ ml  ☐ mcg  ☐ drops  ☐tsp  ☐tablet/capsule  ☐don’t know  ☐ other:_____ |  | ☐ oral  ☐ topical  ☐ IM  ☐ rectal  ☐ IV  ☐ don’t know  ☐ other : ________ | _ _ / _ _ / _ _ | _ _ / _ _ / _ _  ☐Continuing |  |
|  |  | ☐ mg  ☐ g  ☐ ml  ☐ mcg  ☐ drops  ☐tsp  ☐tablet/capsule  ☐don’t know  ☐ other:_____ |  | ☐ oral  ☐ topical  ☐ IM  ☐ rectal  ☐ IV  ☐ don’t know  ☐ other : ________ | _ _ / _ _ / _ _ | _ _ / _ _ / _ _  ☐Continuing |  |
|  |  | ☐ mg  ☐ g  ☐ ml  ☐ mcg  ☐ drops  ☐tsp  ☐tablet/capsule  ☐don’t know  ☐ other:_____ |  | ☐ oral  ☐ topical  ☐ IM  ☐ rectal  ☐ IV  ☐ don’t know  ☐ other : ________ | _ _ / _ _ / _ _ | _ _ / _ _ / _ _  ☐Continuing |  |

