# Annex XI

Timeline

| **Month** | **1** | **2** | **3** | **4** | **5** | **6** | **7** | **8** | **9** | **10** |
| --- | --- | --- | --- | --- | --- | --- | --- | --- | --- | --- |
| **Protocol development** | X |  |  |  |  |  |  |  |  |  |
| **Ethics approval** |  | X |  |  |  |  |  |  |  |  |
| **Site preparation** |  | X | X |  |  |  |  |  |  |  |
| **Patient enrolment** |  |  |  | X | X | X | X | X | X |  |
| **Study closure** |  |  |  |  |  |  |  |  | X |  |
| **Analysis and publication** |  |  |  |  |  |  |  |  | X | X |

1. defined as a child whose growth standard is below –3 z-score, has symmetrical oedema involving at least the feet or has a mid-upper arm circumference < 110 mm) [↑](#footnote-ref-1)

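### The annexed CRF does not match the protocol body in three places: completion status stops at day 16 of 30, the medication table is restricted to grade 3 or 4 symptoms, and no field records gametocytes

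*Protocol*

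**What the plan says.** **Follow-up and completion.** The synopsis has "patients to be followed for 30 days" for both species. Study Procedures schedules visits on days 23 and 30, and section 5.2 includes "Recurrence of parasitaemia within 30 days of follow up". The end-of-study assessment in Annex IX asks whether "The patient completed follow up until day 16". Only a no leads to the list of reasons (second vomiting, early failure, severe G6PD deficiency, withdrawal, loss to follow-up, death, other).

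**Other drugs.** Section 4.4.2 requires regular medication at entry to be recorded on the CRF, and adds: "Any additional medications taken within the follow-up period must be documented in the CRF". All three pages of the CRF medication table are headed with the condition "only if any symptoms with grading 3 or 4 occurred". Annex I lists drugs with antimalarial activity to be avoided, among them doxycycline and sulfamethoxazole.

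**Gametocytes.** Section 5.2 lists "Proportion of Pf patients with gametocytemia on any of the follow up dates". The slide entries in the CRF have a parasite count and, on most pages, a species tick box.

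**Timeline.** Annex XI marks enrolment in months 4 to 9 and "Study closure" in month 9 only.

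**The concern.** An analysis plan can define how data are handled, but it cannot recover what no form collects. Each mismatch bears on a stated endpoint or rule.

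- A 30-day recurrence estimate and late safety reporting both depend on why patients stop attending. If withdrawal, loss and other exits after day 16 all carry the same completed status, the analyst cannot judge whether late dropout is related to outcome.
- An antibiotic with antimalarial activity, taken for a mild illness, could suppress a recurrence. Without drug name and dates, such patients cannot be identified or set aside in a sensitivity analysis.
- The gametocytaemia proportion has no source field, so completing the CRF exactly as designed gives no data for it.

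**Working it through.** No sample-size or power figure is involved. The check sets the protocol body beside its own CRF; the only arithmetic is on days.

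**1. Completion status**

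- Study Procedures counts the later visits from day 2: 2 + 7 = 9, 2 + 14 = 16, 2 + 21 = 23, 2 + 28 = 30. This reproduces the stated visit days.
- The completion item stops at day 16, so it leaves out 30 − 16 = 14 days, or 14/30 = 47% of follow-up, and two visits (days 23 and 30).
- Take a patient who attends on day 16 and withdraws on day 20. The answer to the completion item is yes, the reason list stays closed, and the day 23 and day 30 pages are blank. A patient who is lost to follow-up on day 20 produces the same record.
- The day 23 and day 30 pages both reuse item numbers 24 and 25, already used on the day 12 page. This suggests, as an inference only, that they were added later and the end-of-study item was not updated.

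**2. Medication**

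- Required by section 4.4.2: regular medication at entry, and any additional medication during follow-up.
- Provided by the CRF: the day 0 page has no medication field. The medication table opens only after a grade 3 or 4 symptom. The symptom form has a tick box for a prescribed drug at any grade and a free-text line for actions taken, but neither requires name, dose or dates.
- Rescue Treatment says rescue drugs are noted on the CRF, but the unscheduled-visit pages have no treatment field.
- Take a patient given doxycycline for a mild illness on day 10. At most a tick and an optional free-text note result. If the patient obtained the drug without reporting a symptom, nothing prompts a record.

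**3. Gametocytes**

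- CRF slide entries exist for days 0, 1, 2, 6, 9, 12, 16, 23, 30 and two unscheduled visits. Each has a count per red or white cells. None separates gametocytes from other stages.
- The Microscopy section does not mention gametocytes. So none of the approximately 160 planned falciparum patients has a field for this endpoint.
- Falciparum patients take PQ on day 3, so the day 1 and day 2 slides precede it and the later visits follow it. One proportion over all follow-up dates does not separate the two periods.
- The first falciparum visit after PQ is stated inconsistently: day 9 in Study Procedures and in Treatment & sample collection, day 12 in the falciparum row of the schedule table.

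**4. Timeline (secondary)**

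- A patient enrolled in month 9 reaches day 30 in month 10, except perhaps one enrolled at the very start of the month. Closure is marked for month 9 only.

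**The case against.** The strongest reply is that the CRF collects more than its end-of-study page suggests. That is right, and it limits the point in several ways.

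- **A reader might infer that the CRF ends follow-up at day 16.** It does not. The day 23 and day 30 pages hold visit date, temperature, slide, parasite count, species and Hb.
- **A reader might infer that patients lost late would be counted as cured.** No section says so. The last attended visit is dated, so a censoring time is available. A death could also be entered as a fatal outcome on the symptom form. What is missing is the completion status and the reason for leaving.
- **A reader might infer that drugs for mild illness leave no trace.** The tick box and free-text line give an unstructured place for them. Regular medication, self-obtained drugs, and required names, doses and dates remain uncovered.
- **A reader might infer that gametocytaemia could never be obtained, or that the endpoint is meant to estimate a PQ effect.** Slides are taken at every follow-up visit, so one added field would supply the result. No objective or analysis in the protocol uses the endpoint to estimate an effect of PQ; it is descriptive and does not appear in the synopsis. Reporting by visit is a matter of clarity, not the correction of a stated estimand.
- **A reader might divide the target of 50 + 160 = 210 by six enrolment months and conclude that 35 patients lose their late visits.** That assumes even accrual in a seasonal disease and reads a month-level planning chart as a rule for dropping visits. The protocol supports neither.

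The three mismatches survive these limits. The absence of a day 3 page in the CRF is a related gap, but the point does not rest on it.

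**Conclusion.** The point holds as a set of conflicts between the protocol body and its own CRF. Followed as written, the forms would:

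- record patients who leave on days 17 to 30 as complete with no reason (14 of 30 days, 47%, and two visits);
- leave regular medication, and additional medication in patients without a grade 3 or 4 symptom, without any required name, dose or dates, contrary to section 4.4.2;
- leave the falciparum gametocytaemia endpoint with no source field.

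These should be corrected, but they do not undermine the study: Hb and parasitaemia still have CRF pages at days 23 and 30. How many patients would be affected cannot be stated, because the protocol gives no expected dropout, drug use or gametocyte carriage. The conclusion assumes that the annexed CRF is the form to be used, and that no separate log or laboratory form collects these items; the protocol mentions none. The timeline remark is secondary.

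**What to change.** - **End of study:** ask completion at day 30, with date of last contact and the existing list of reasons.
- **Medication:** remove the grade 3 or 4 condition from all three pages of the table, and add a regular-medication item on day 0.
- **Gametocytes:** add a gametocyte result to each falciparum slide entry and report gametocytaemia by visit, so that days 1 and 2 stand apart from visits after PQ. First reconcile the falciparum visit day, given as day 9 in the text and day 12 in the schedule table.
- **Timeline:** move closure in Annex XI so that it allows for the day 30 visits of the last patients enrolled.

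The cost is a few CRF fields, one deleted heading condition, one timeline cell and a small amount of extra data entry, on slides and visits already planned. No new samples are needed.

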# Assessment of variables and statistical methodology

## Safety endpoints

- Proportion of patients with severe anaemia (Hb<7g/dl)
- Proportion of patients receiving blood transfusion
- Fractional change in Hb between baseline and day 6, 9,12,16, 23 and 30 (incl. proportion of patients with >25% drop in Hb between the timepoints)
- Proportion of patients with anaemia less than 7g/dl on day 3 and day 9
- Proportion of patients with adverse and serious adverse events

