**Late parasitological failure**

Presence of parasitaemia on any day between day 7 and the last day of follow up with axillary temperature < 37.5 ºC in patients who did not previously meet any of the criteria of early treatment failure or late clinical failure

#

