***If no***

Principal reason for premature termination:

☐Patient vomited the study drug a second time and received rescue treatment before PQ was given

☐Early Treatment failure before PQ was given

☐Patient found to be severely G6PD deficient and excluded before PQ treatment was given

☐Patient withdrew consent

☐Lost to follow up

☐Death

☐ Other: please specify………………………………………………

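### The end-of-study form sets completion at day 16 although follow-up runs to day 30, so no reason is recorded for a patient who leaves on days 17 to 30

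*Protocol*

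**What the plan says.** The End of study assessment in Annex IX has a single completion item: "The patient completed follow up until day 16", answered *Yes* or *No*. Below it, under the *No* branch only, comes the item "Principal reason for premature termination". Its options are a second vomiting of study drug, early treatment failure, severe G6PD deficiency, withdrawal of consent, loss to follow-up, death and other. The first three are worded as events before primaquine was given. The others can happen at any time.

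Elsewhere the protocol works to day 30:

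- Synopsis, Study Duration, in the same words for *P. falciparum* and *P. vivax*: "patients to be followed for 30 days".
- Section 4.4, Study Procedures, schedules the reviews after day 16 at "21 days (day 23) and 28 days (day 30").
- Section 5.1, Safety endpoints: "Fractional change in Hb between baseline and day 6, 9,12,16, 23 and 30".
- Section 5.2, Efficacy endpoints: "Recurrence of parasitaemia within 30 days of follow up".
- Annex VII defines late parasitological failure as "Presence of parasitaemia on any day between day 7 and the last day of follow up" (in patients without fever or an earlier failure).

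The same case record form has separate visit pages for day 23 and day 30.

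**The concern.** A disposition page should say, for each patient, whether planned follow-up was completed and, if not, why and when it ended. Here the page stops at day 16, while visits and endpoints continue for two more weeks. Patients who leave in those weeks meet the form's definition of completion, so the reason list is never reached.

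The primary objective is to describe side effects of unsupervised primaquine. Whoever reads the results will want to know whether a patient missing on day 23 or day 30 moved away, withdrew, fell ill or died. If the form does not ask at the time, no later analysis rule can supply the answer.

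**Working it through.** The plan states no figure to reproduce. The check sets the passages side by side and makes a few counts.

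**1. Period not covered.** The completion item ends at day 16 (Annex IX). Follow-up ends at day 30 (Synopsis; section 4.4). Days not covered: 30 − 16 = 14, and 14/30 = 47% of follow-up.

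**2. Visits not covered.** Days 23 and 30.
- Vivax and mixed patients have six visits after primaquine starts on day 3 (days 6, 9, 12, 16, 23, 30; section 4.4.1). Two of the six are not covered.
- Falciparum patients have four (days 9, 16, 23, 30; section 4.4.1). Two of the four are not covered. The schedule table marks day 12 instead of day 9 for this group, which leaves the count unchanged.

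**3. What those visits feed.** The schedule table plans slides on days 23 and 30 for all patients, and haemoglobin on those days for vivax and mixed patients. Section 7 also plans a relative risk for a haemoglobin drop of more than 25% between days 23 and 30 in patients given 14 days of primaquine.

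**4. One patient followed through the form.** A patient attends day 16, misses days 23 and 30 and cannot be found. Under section 4.4.4, which ties loss to follow-up to scheduled visits and sets no day-16 limit, this patient is lost. On the closing page the truthful answer is *Yes*, and the option for loss to follow-up is not reached. The two parts of the protocol classify the same patient differently.

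**5. Could another field hold the information?**
- Visit pages for days 23 and 30: these carry a visit date and yes/no items for the finger prick and slide, so a missed visit can be seen. They give no reason.
- Symptom reporting form: this has a fatal outcome, so a death entered as an adverse event is captured.
- Withdrawal or loss after day 16: the form has no field for either.
- Date of last contact: none. The last attended visit can be derived from the visit pages, but a contact outside a visit cannot.

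**6. Number of records affected.** The protocol gives no dropout rate. Assume, for illustration only, that 5%, 10% or 20% leave on days 17 to 30, and take the targets in section 8 (about 50 vivax and 160 falciparum):
- vivax: 50 × 0.05 = 2.5, 50 × 0.10 = 5, 50 × 0.20 = 10;
- falciparum: 160 × 0.05 = 8, 160 × 0.10 = 16, 160 × 0.20 = 32.

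These are counts of patients who would have no exit reason on the closing page. They do not measure bias in any endpoint.

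**The case against.** **The tick is true as worded.** A *Yes* says only that day 16 was reached, and day 16 is the last day of the 14-day primaquine course. That stands as a reading of the item. It does not rescue the page, which is headed as the end of the study and is also used for falciparum patients. They take a single dose on day 3 and make up about 160 of the 210 planned patients. The item looks like a line that was not updated: the day-23 and day-30 pages reuse item numbers 24 and 25 from the day-12 page, although the day-16 page already runs to item 30. This is an inference from the numbering, not something the protocol states.

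**A reader might infer that 30-day recurrence is biased downward**, because patients ticked as complete would count as recurrence-free. The protocol does not support this. Nothing ties the recurrence endpoint to the tick, and section 7 describes neither a recurrence analysis nor a set of completers. Recurrence would be read from slides, and the day-23, day-30 and unscheduled pages record the visit date, whether a slide was taken and the result. A patient not seen on day 30 has no day-30 slide, which differs from a negative one. In addition, section 9.7 has data collected before a withdrawal of consent destroyed, so on that text a patient who withdraws late would not stay in the data as a completer.

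**A reader might also infer that late deaths go unrecorded.** They are absent from the disposition page only. The symptom form can hold them, section 4.4 collects adverse events at every visit, and section 9.1 provides for a safety board.

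**Censoring belongs to the analysis plan.** Agreed: the estimator and the censoring rule for recurrence can be set there, and nothing is asked of the protocol on that point. What the form collects is a different matter, because an analysis plan cannot recover reasons that were never asked for.

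**Conclusion.** The closing form is wrong as written. It sets completion at day 16, against 30 days of follow-up everywhere else in the protocol. Completed exactly as printed, it marks patients lost or withdrawn on days 17 to 30 as having completed and records no reason. A late death is missing from the disposition record, though not necessarily from the safety data. The gap covers 14 of 30 days and two scheduled visits for every patient.

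The conclusion rests on the printed text alone and needs no assumed rate. How many patients are affected depends on late dropout, which the protocol does not give. No size of bias in recurrence or haemoglobin should be claimed. What is lost is the reason for leaving and the date of last contact.

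**What to change.** In Annex IX, End of study assessment:

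- Change the completion item so that it asks about follow-up to day 30.
- Whenever day 30 was not reached, ask for the principal reason, using the existing list, and for the date of last contact.
- If the day-16 milestone is wanted, keep it as a separate tick that does not control whether a reason is asked.

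The cost is one changed line and one date field, plus one tick box if day 16 is kept. No visit, sample, treatment or endpoint changes.
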